## Methods

### Design

A mono-center open label RCT with a two parallel group design will be conducted. A total of 105 eligible participants will be randomly allocated to either TAU with the addition of FNC or TAU alone, after the first baseline assessment. All participants receive treatment as usual within a forensic mental health care institute at the time of the baseline assessment. Participants in the FNC condition are offered an additional intervention – Forensic Network Coaching – consisting of two-monthly appointments with a forensic network coach. Assessments will take place before randomization at baseline and every 3 months after baseline assessment until the final assessment at 12 months of treatment. The follow-up assessment will be conducted at 18 months after baseline assessment. Number of crime occurrences and recidivism rates, will be determined at 12 months and 36 months after baseline assessment*.* The effectiveness of FNC will be examined at 12 and 18 months after baseline assessment. Approval for the study protocol was given by the Medical Ethics Committee of the VU University Medical Center (registration-number NL60308.029.17). The study is registered at the Netherlands Trial Register, part of the Dutch Cochrane Center (NTR7163). Figure 1 provides an overview of the trial design.

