### Procedure

#### Recruitment and consent

Patients will be recruited at all outpatient sites of Inforsa Forensic Mental Health Care, a department of Arkin Mental Health Care, a large mental health care institute in Amsterdam, the Netherlands. Recruitment is planned for 2 years. Patients will be screened for eligibility by a clinician and researcher during treatment. Researchers will inform and stimulate clinicians to refer patients by participating in team meetings, spreading information flyers, reminding clinicians, spreading newsletters and monthly presentations. When eligibility is assumed, the clinician will introduce the study to the patient to check whether the patient is interested in participating. After a patient expresses interest, more extensive screening between the clinician and researcher will take place.

Subsequently, the first recruitment appointment will be scheduled with eligible patients who agreed to be approached by a researcher. During the first appointment the patient will be screened for eligibility by a researcher. Furthermore, patients’ motivation for participation will be assessed. All eligible patients receive a written study information letter. The content of the study information letter will also be explained by a researcher. Depending on the preferences of the patient, the second appointment for the screening interview, informed consent and baseline assessment will be planned. The second appointment will take place at least a week after the first face-to-face appointment so enough time for consideration is provided. In addition, the researcher asks whether the patient agrees to be approached by a research assistant by phone, in order to check agreement with participation, to answer questions and to plan appointments for follow-up assessment.

During the second appointment, informed consent will be signed by all patients. After informed consent, baseline assessment will take place in which all in- and exclusion criteria are checked again by a researcher. If necessary - to decrease the burden for participants - baseline assessment will be divided into multiple appointments. The baseline assessment should preferably be completed within 1 month after informed consent.

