#### Randomization and procedure

Independent research assistants and research associates - not familiar with the patient or responsible for any kind of mental health care - of the research department of Inforsa are involved in the recruitment procedure, randomization, data collection and data management of this study. Randomization will be performed at an individual level, stratified by forensic outpatient care site. We aim to carry out randomisation after completion of (the first half of) the baseline assessment. A computer-generated block randomization schedule provided by Castor Electronic Data Capture (EDC) is used. The allocation ratio will be 1:1 to ensure that an equal number of patients will be allocated to either TAU or FNC. Researchers will not have access to the randomization schedule and will be blind to block size and order. Blinding for treatment after randomization is not possible, as the content of treatment will be clear to both patients and therapists. Blinding researchers is not feasible due to different assessments of the conditions and required coordinating activities - referring patients to FNC and monitoring - of researchers during the FNC intervention.

The experimental intervention starts preferably within 2 months after completion of the baseline assessment and ends 12 months after baseline assessment. During the intervention, patients in both FNC and TAU condition will be assessed at 3, 6 and 9 months after baseline assessment. At the end of treatment (12 months) and follow-up (18 months) additional questionnaires will be administered. Figure 1 provides an overview of the trial design. Two supplemental measures, the Work Alliance Questionnaire (WAV-12) and a qualitative interview, will only be assessed in the experimental group. Table 1 provides an overview of all instruments and the corresponding time of assessment.

**Table 1 Tab1:** Overview of outcome measures, instruments and time of assessment from baseline in months

Outcome	Concept	Instrument	baseline 0	3	6	9	end 12	follow-up 18	36
**Primary**	Mental wellbeing	MHC-SF	•	•	•	•	•	•	
**Secondary**	Psychiatric functioning^a^	HoNOS	•	•	•	•	•	•	
	Criminal recidivism	SRD	•				•	•	
		IPOL					•		•
		JDS					•		•
	Substance abuse	MATE 2.1	•	•	•	•	•	•	
	Quality of life	MANSA	•	•	•	•	•	•	
	Social network	NGI-method	•				•	•	
	Social support	SSL	•				•	•	
	Loneliness	Loneliness Scale	•				•	•	
	Self-sufficiency	SSM-D	•	•	•	•	•	•	

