## Statistical analysis

An intention-to-treat analysis will be included in the data analyses of the primary outcome measure (mental wellbeing) and secondary outcome measures (psychiatric functioning, criminal recidivism, substance abuse, quality of life, social network, social support, loneliness and self-sufficiency). Besides, subgroup analyses will be conducted on the protocol completers sample. Generalized Linear Mixed Models (GLMM) in Statistical Package for the Social Sciences (SPSS) will be used to model all continuous outcome measures, considering the distributional characteristics of the data. If the normal distribution assumption is violated, resampling methods will be used to transform data into a normal distribution or appropriate non-parametric tests will be used. Generalized Estimating Equations (GEE) will be used to analyze the categorical outcome measures. The main between-group effect (TAU versus FNC) and the interaction effect (group * time) will be analyzed whilst correcting for baseline assessment. Outcome data of all assessments will be included in the analyses to examine the differences in the development in time between both groups. The criminal recidivism data will be analyzed using Survival Analysis and corrected for time at risk. Missing data will be addressed using multiple imputation or statistical techniques that control for missingness-at-random.

To assess the magnitude of treatment effects on the primary outcome and secondary outcomes, Cohen’s *f* effect size will be calculated. Effect sizes of *f* = 0.40 are considered large, effect sizes of *f* = 0.25 are considered moderate and effect sizes of *f* = 0.10 are considered small (Cohen, 1988).

Moderator analyses will be used to examine potential moderators of treatment outcome by adding potential moderators as covariates of factors to the GLMM/GEE analyses. Furthermore, multilevel mediation models will be carried out to examine potential mediators of treatment outcome. At last, appropriate statistical methodology in ATLAS.ti will be used for the analyses of the qualitative data [111].

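### The protocol lets randomisation fall midway through the baseline assessment, so outcome baselines or the eligibility re-check could be obtained with the arm known

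*Protocol article*

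**What the plan says.** The protocol article describes the order of baseline and allocation in three places.

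- Design: "Assessments will take place before randomization at baseline and every 3 months after baseline assessment". The same section says that participants "will be randomly allocated to either TAU with the addition of FNC or TAU alone, after the first baseline assessment".
- Randomization and procedure: "We aim to carry out randomisation after completion of (the first half of) the baseline assessment".
- Recruitment and consent: if needed to limit burden, "baseline assessment will be divided into multiple appointments", preferably finished within 1 month of consent. The re-check of eligibility belongs to this assessment: "After informed consent, baseline assessment will take place in which all in- and exclusion criteria are checked again by a researcher". There is also a screen before consent: "During the first appointment the patient will be screened for eligibility by a researcher".

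The randomisation section states that patients, therapists and researchers are not blinded after allocation. Under Statistical analysis, the group effect and the group-by-time interaction "will be analyzed whilst correcting for baseline assessment". The primary outcome section defines the main measure as the between-group difference in MHC-SF from baseline to 12 months.

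**The concern.** A baseline value is safe to adjust for because treatment assignment cannot have influenced it. That protection is lost once the patient, or the researcher rating the patient, knows the arm. The MHC-SF is self-reported, and hope or disappointment about the allocation could move it. The HoNOS, a key secondary outcome, is scored by a researcher who is unblinded after allocation. A baseline shifted in this way enters the treatment estimate directly, and the bias can run in either direction.

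The eligibility re-check is exposed in the same way. SSM, MANSA, MINI-plus and HoNOS serve both as eligibility instruments and as baseline instruments. A failure discovered after allocation would have to be handled by someone who knows the arm.

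This is more than a detail left to a fuller document. The article itself states a rule that permits mid-baseline allocation, and it sits badly with the article's own Design section.

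**Working it through.** **Comparing the sections.** The plan gives no figure for this point, so the first check is textual.

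1. Design places baseline assessments before randomisation. The procedure section allows randomisation once the first half is done. Both cannot be the operating rule for a patient whose baseline is split.
2. The other Design phrase, allocation after the first baseline assessment, does not settle the matter. It can mean the whole of the first assessment wave or only the first session.
3. A split is foreseen in the recruitment section. The Discussion adds pressure towards early allocation, because referral to coaching takes time and circumstances may change. Mid-baseline allocation is therefore a realistic event.
4. Table 1 lists at baseline the MHC-SF, HoNOS, SRD, MATE, MANSA, network interview, SSL, Loneliness Scale and SSM-D, together with MINI-plus, CTQ-SF, ASQ, SCIL and HIT-Q. No section assigns any of these to a half.
5. Coaching starts preferably within 2 months after baseline completion. The exposure is therefore to knowledge of the arm rather than to coaching itself.

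**Illustrating the size.** Inputs:

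- Within-person correlation ρ = 0.50 (Sample size section).
- Planned effect f = 0.20 (Sample size section). For two equal arms, d = 2f = 0.40.
- p, the share of patients giving the MHC-SF baseline after allocation: 0.25 to 0.50. **Assumed.**
- δ, the between-arm shift in baseline MHC-SF among those patients caused by knowing the arm, in SD: 0.1 to 0.3. **Assumed.**

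The recorded baseline difference between arms is displaced on average by pδ. With equal SDs at both times, the adjustment slope is about ρ, so the adjusted effect is displaced by

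bias ≈ −ρ × p × δ.

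| p | δ (SD) | size of ρpδ (SD) | share of d = 0.40 |
|---|---|---|---|
| 0.25 | 0.1 | 0.5 × 0.25 × 0.1 = 0.0125 | 3.1% |
| 0.25 | 0.3 | 0.5 × 0.25 × 0.3 = 0.0375 | 9.4% |
| 0.50 | 0.1 | 0.5 × 0.50 × 0.1 = 0.025 | 6.3% |
| 0.50 | 0.3 | 0.5 × 0.50 × 0.3 = 0.075 | 18.8% |

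If knowing the arm raises reported wellbeing in the coaching arm relative to control, δ is positive and the benefit is understated. With the opposite sign it is overstated. Only the product pδ matters: each 0.1 SD of average displacement moves the adjusted effect by 0.05 SD, or 12.5% of 0.40.

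**The case against.** The strongest reply is that no harm is shown. Nothing puts the MHC-SF, the HoNOS or any eligibility item in the second half, and the order of instruments in a battery is the kind of detail a journal article leaves to its full protocol. The MHC-SF may well come first in practice. This stands as a limit on what can be claimed about bias. It does not remove the point, because the permission to allocate at mid-baseline is stated and the Design section says otherwise.

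The second reply concerns eligibility. Clinician and researcher screen patients before consent, and the baseline step is a re-check, so late failures should be few. A reader might infer that such failures become exclusions after randomisation, made by unblinded staff. The documents do not support that: no section says a patient failing the re-check after allocation is removed, and the analysis is by intention to treat. What remains is that the plan does not ensure the re-check precedes allocation.

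Third, a reader might put the bias higher. Under a pure change-score estimator the displacement is pδ, so p = 0.50 and δ = 0.3 give 0.15 SD, or 0.15 / 0.40 = 37.5% of the planned effect. The definition of the main outcome leaves some room for that estimator, but the analysis section specifies correction for baseline. The figure also takes the worst value of both assumed inputs. A p of 0.50 would need half the patients to have a split baseline, to be allocated between sessions and to meet the MHC-SF in the later one, whereas splitting is foreseen only where necessary.

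Finally, early randomisation has a stated reason in the long referral process. That trade-off is legitimate, and a remedy should respect it.

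**Conclusion.** The point holds as a stated rule that can bias the result, together with an inconsistency between the Design section and the randomisation section. It does not show that the trial's baselines are biased. Whether any outcome baseline or eligibility item is collected after allocation cannot be told from the article, and the size of any effect is unknown. Under the assumed ranges, with the stated correlation of 0.50 and a baseline-adjusted analysis, the displacement would be about 0.01–0.08 SD, or 3–19% of d = 0.40, in either direction. If the MHC-SF is always completed before allocation, it is zero for the primary outcome. The matter deserves correction because analysis cannot identify the affected values unless their timing is recorded, and because the remedy is cheap.

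**What to change.** Reconcile the Design and randomisation sections with one rule, for example: *Allocation is released only after the eligibility re-check and the baseline of every primary and secondary outcome measured at baseline are complete, the MHC-SF first, then the HoNOS and the other secondary outcomes.*

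Only instruments that are administered at baseline alone and are neither outcomes nor eligibility measures may be left to a later session, such as CTQ-SF, SCIL and HIT-Q. The ASQ should not be deferred: it is self-reported, listed among the mediators and moderators, and repeated at 12 months.

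For patients already randomised mid-baseline:

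- record the date and order of each baseline instrument relative to allocation;
- flag values collected after allocation;
- keep all randomised patients in the intention-to-treat analysis;
- run a sensitivity analysis that treats the flagged values as missing.

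Making the sensitivity analysis the main one is debatable in a sample of 105.

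The cost is a reordered battery and a short delay to allocation for patients whose baseline is split. The delay is not quantified in the documents, but the plan already aims to finish baseline within 1 month of consent. Most of the battery would now precede allocation. The deferrable part is still material: CTQ-SF and HIT-Q alone account for 27 + 54 = 81 items, with the SCIL in addition, so some relief of burden and reasonably early randomisation are kept.

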### Interventions

#### Treatment as usual (TAU)

The vast majority of potential participants receives forensic FACT which can include specific therapeutic interventions such as social work, psychotherapy (e.g. CBT, EMDR) and pharmacotherapy. We will include patients at the forensic outpatient care site not receiving forensic FACT as well if social network-related problems are present and social participation is limited. All forensic outpatient care sites include psychotherapies and treatment models that are part of the treatment guidelines for forensic outpatients.

In short, forensic FACT is a widely used treatment model developed for forensic outpatients with severe psychiatric disorders, combined with multiple social problems [19]. The primary goal of forensic FACT is to enhance (mental) wellbeing as well as to reduce the risk of criminal recidivism. Forensic FACT teams consist of different health care professionals such as psychiatrists, nurses specialized in psychiatric problems, psychologists, job coaches and social workers. Treatment is delivered within the community of the patients. In general, individual face-to-face appointments between professionals and patients take place weekly at the institution or at a patients’ home. The intensity of the treatment is customized to the patient’s needs. If necessary, for example in case of (the prevention of) a crisis, the frequency of appointments can be increased and more professionals can be involved. Furthermore, CBT or psychotherapeutic interventions are indicated and performed by psychologists based on the patients’ needs and their individual risk assessment of criminal recidivism. Examples of common interventions are aggression regulation therapy [57], CBT for alcohol- or drug-use disorders [58], community reinforcement approach [59], delict analysis [60] and motivational interviewing [61]. CBT interventions and psychotherapy consist of weekly face-to-face appointments at the participating site. Besides, interventions may also be offered online or blended.

Care professionals of all patients included in the study (TAU and FNC) will be stimulated by the research team to focus on improvement of the social network during treatment. After baseline and follow-up assessments professionals will receive an e-mail with information about a brief social network intervention and to inform them about their patient’s participation. TAU might be discontinued or finished during the course of the study, therefore the type and duration of treatment will be monitored. No treatments are withheld from patients in TAU except Forensic Network Coaching.

#### Forensic network coaching (FNC)

In the experimental group a social network intervention - Forensic Network Coaching (FNC) - will be added to TAU during a period of maximum 12 months. FNC is an informal coaching or mentoring program that aims to improve (the quality of) social networks, social support and social participation. A carefully selected volunteer - a forensic network coach - is trained to conduct a structured intervention ‘Of course, a network coach!’ [62].

The intervention ‘Of course, a network coach!’ is included in an extensive list of effective social interventions by Movisie, a Dutch knowledge institute that focuses on social issues. Although empirical research has not been conducted, promising results have been published. A qualitative study shows that participants gained self-confidence, energy and social skills after completing the coaching intervention [63]. Furthermore, the intervention is based on the TO GROW (Goal Reality Options Will) model of coaching [64] and on Solution Focused (Brief) Therapy (SFT) [65, 66]. SFT is known to be an effective intervention in reducing psychiatric problems [67–69], improving mental wellbeing and social- and problem-solving skills [55, 70–73].

The intervention consists of ten steps: step 1 to 3, the Orientation phase, focuses on exploring patients’ wishes regarding the social network and determining goals. Subsequently, in the Thinking phase, step 4 and 5, both coach and patient will explore possible ways to improve or rebuild the social network. Lastly, in the Action phase, step 7 to 10, formulated plans will be executed. Every plan involves three components: 1) explanation for the coach, 2) a patient worksheet, 3) a practical and theoretical form for the coach. However, due to the characteristics of the forensic population - motivational challenges, disabilities and complex psychiatric problems - this intervention will merely be used as a theoretical guideline and tool for coaches while working on the improvement of the social network of participant. The intervention will be adjusted to the needs, pace and possibilities of the participant.

During FNC, patients are matched to a forensic network coach based on their personal preferences, characteristics and interests, after an intake appointment with De Regenboog Groep.^1^ Prior to the intake, necessary information regarding the social situation of the patient is provided by a member of the research team – a procedure for which written consent is given. If matching is successful - both coach and patient agree with the match - coaching appointments take place once every 14 days. Between appointments, coaches and patients may engage in ear-to-ear or screen-to-screen contact. Within the first three to 6 months of FNC, coaches are stimulated to focus on enhancing motivation and building a working alliance with their patient. The following months will be used to draft personal goals and gaining new social experiences. Forensic network coaches visit patients in their own social environment. Besides, coaches and patients are stimulated to participate in new social activities. Evaluation of FNC takes place every 3 months and after completion of FNC, at 12 months of coaching. Both coaches and participants can decide to continue the contact after completion of FNC.

#### Forensic network coaches

The forensic network coach is a carefully selected and trained volunteer who can be a role model and a supportive network member for the patient. The relationship between the coach and patient is called informal, meaning that coaches are non-professional volunteers that do not receive payments for their services. Furthermore, the relationship between a coach and patient is based on equivalence, confidence and liberty. Coaches are not involved in the treatment as usual.

Forensic network coaches will be provided by De Regenboog Groep, experienced in delivering coaching programs. De Regenboog Groep is responsible for the selection, training, matching and supervision of forensic network coaches. All coaches receive training in basic coaching skills, the social network intervention and on how to provide informal care within a complex forensic population. Coaches receive a manual with a worksheet of the intervention ‘Of course, a network coach!’. In addition, to ensure treatment fidelity, coaches will receive regular group supervision meetings. All coaches will be monitored by a professional of De Regenboog Groep during the coaching phase.

